### Statistical analysis

The main objective is to evaluate the predictive value of the presence of ctDNA post-operatively on RFS. The RFS will be described by the Kaplan–Meier method, and compared according to the presence or absence of ctDNA post-surgery using the log rank test. A multivariate Cox regression model will be used to calculate the hazard ratio and 95% confidence interval (CI). As this is a cohort study, the results will be adjusted for baseline patient characteristics and the type of adjuvant therapy. To this end, bivariate analyses will be performed to identify variables related to the RFS. Variables yielding a *p*-value < 0.10, and the presence of ctDNA post-surgery will be included in the multivariate model. Results will be presented as hazard ratios with 95% CIs.

The same analysis will be performed for ctDNA presence pre-surgery, for the number of copies of mutant DNA per ml of plasma pre- and post-surgery, and for absolute and relative variations of the quantity of mutated DNA between pre- and post-surgery.

The impact of ctDNA evolution during follow-up on RFS will be evaluated using time-dependent survival models, by considering mutated DNA copy number as a time-dependent variable in the Cox model. This analysis will be adjusted for baseline patient characteristics and for the type of adjuvant therapy to assess whether the course of ctDNA during follow-up is an independent prognostic factor for survival.

To determine whether the predictive value of the course of ctDNA varies according to clinical and tumour characteristics at baseline, interaction tests will be performed.

Distant metastasis-free survival will be analysed using the same approach as for RFS. Melanoma-specific survival will also be analysed using the same approach, but considering death unrelated to the disease as a competing risk. Consequently, specific survival will be described as cumulative incidence according to the Kalbfleisch-Prentice method, and compared using Gray’s test. Bi- and multivariate analysis will be performed using the Fine and Gray subdistribution model.

Baseline characteristics of the study population will be compared between patients with and patients without detectable ctDNA pre- and/or post-operatively. Qualitative variables will be compared using the chi square or Fisher’s exact test, and quantitative variables using the Student t or Mann–Whitney U test, according to whether the distribution of the variable is normal or not. Normality will be tested using the Shapiro–Wilk test. A multivariate logistic regression model will be fit to determine the characteristics that best distinguish the two populations. The discriminant power of the model will be determined using the area under the receiving operating characteristic (ROC) curve. In patients with no detectable ctDNA either pre- or post-operatively, the course of quantification of ctDNA will be described by repeated measure ANOVA using the mixed linear model, to take account of the correlation between measures in a same patient. Time will be considered as a fixed effect, and the patient as a random effect. The analysis will be performed in patients who have progressive disease, and those who do not.

The cut-off timepoint for this analysis will be the date of progression or end of follow-up. The values analysed will be number of copies of mutant DNA, taking account of all values obtained since inclusion.

All statistical analyses will be performed using SAS version 9.4 (SAS Institute Inc., Cary, NC, USA). A *p*-value < 0.05 will be considered statistically significant.

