### Sample size calculation

Our hypothesis is that 25% of patients will have detectable ctDNA post-operatively, i.e. within 2 to 3 weeks after surgery [20].

Recurrence-free survival at 24 months in this population, based on key studies of adjuvant therapies, can be estimated at 70% (upper limit, to ensure a good statistical power) [1, 2, 24].

Based on an inclusion period of 24 months, an alpha risk of 5% and statistical power of 90%, a total of 124 patients would be required to achieve a hazard ratio of 2.5 [18, 20]. By considering 10% of patients lost to follow-up at 24 months or not analysable, then a total of 136 patients are necessary.

It is expected that almost all patients with stage IIIc/IIId/IV melanoma who are pre-included will subsequently be definitively included. Conversely, we estimate that around 70% of patients with stage IIIa-IIIb melanoma who are pre-included will have negative sentinel lymph nodes and therefore, will not be eligible for definitive inclusion. In view of the active pool of patients, we expect that stage IIIa-IIIb patients will account for 25% of all pre-included patients. Thus, to achieve definitive inclusion of 136 patients, we estimate that 165 patients will need to be pre-included.

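### The promised adjustment of the RFS hazard ratio for baseline characteristics and adjuvant therapy is left to a bivariate p<0.10 screen that, at about 37–46 events, does not guarantee that therapy or stage enters the model

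*Protocol article*

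**What the plan says.** The Statistical analysis section compares RFS by post-surgery ctDNA status with a log-rank test and estimates the hazard ratio in a multivariable Cox model. Because the study is a cohort, it states that "the results will be adjusted for baseline patient characteristics and the type of adjuvant therapy". No condition is attached.

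The next sentence gives the method: "To this end, bivariate analyses will be performed to identify variables related to the RFS". Variables with a bivariate p-value below 0.10 "and the presence of ctDNA post-surgery will be included in the multivariate model". So ctDNA is the only term sure of a place. Therapy is named in the promise but not in the entry rule, and stage is not named as an adjustment variable at all.

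The same analysis is reused for pre-surgery ctDNA, for mutant copy number and for its pre-to-post change. Distant metastasis-free survival follows the same approach, and melanoma-specific survival follows it with a competing-risks model. The time-dependent analysis repeats the promise to adjust for baseline characteristics and therapy but mentions no screen.

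No event count is stated. It has to be derived from the Sample size calculation section.

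**The concern.** The stated aim and the stated method can part company. Whenever therapy has p≥0.10 against RFS, the rule leaves it out and the reported hazard ratio is not adjusted for it.

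The screen also tests only half of what makes a confounder. A confounder is related to both the exposure and the outcome, and the rule looks only at the outcome. The Background itself gives reasons to expect the other link: it says that ctDNA concentration follows tumour burden, and that baseline ctDNA went with more nodal involvement and high LDH. Disease extent can therefore be named now as a covariate.

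At stake is how the adjusted hazard ratio can be read. With few events, chance largely decides whether a moderate prognostic factor gets in. The adjustment set could then differ between RFS, DMFS and the pre-surgery analyses, so that their hazard ratios would not be like for like. The usual confidence interval also takes no account of the selection step.

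**Working it through.** **Reproducing the plan's sample size.** Inputs from the Sample size calculation section: "25% of patients will have detectable ctDNA post-operatively"; 24-month RFS 70%; alpha 5% (taken as two-sided) and power 90%; "a total of 124 patients would be required to achieve a hazard ratio of 2.5".

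Freedman's formula with k = 1/3 (ctDNA-positive to ctDNA-negative):

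events = (1.960 + 1.282)² × (1 + 2.5/3)² / [(1/3) × (2.5 − 1)²] = 10.507 × 3.361 / 0.75 = 47.1

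If 70% is the RFS of ctDNA-negative patients, RFS in positives is 0.70^2.5 = 0.41, and the event fraction is 0.75 × 0.30 + 0.25 × 0.59 = 0.3725. Then N = 47.1 / 0.3725 = 126.4, or 127. That is within 3% of 124, so the design is understood. (Schoenfeld's formula needs 67 events and N = 180, and does not reproduce 124.)

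**Events available.** Each patient leaves at 24 months, so the 24-month count is the relevant one.
- 70% read as whole-cohort RFS: 124 × 0.30 = 37.
- 70% read as ctDNA-negative RFS: 124 × 0.3725 = 46.
- If all 136 contributed: 136 × 0.30 = 41 to 136 × 0.3725 = 51.

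**Chance that the screen drops a covariate.** For a binary covariate with share p, d events and hazard ratio HR, the test statistic is approximately normal with mean m = √(d·p(1−p)) × ln HR and variance 1. The variable is dropped when |Z| < 1.645:

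P(drop) = Φ(1.645 − m) − Φ(−1.645 − m)

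Example: d = 37, p = 0.5, HR 1.5 gives m = √9.25 × 0.405 = 1.23 and P(drop) = 0.66.

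The documents give no RFS hazard ratio for stage and no direct contrast between therapies, so the values below are assumptions. The one documentary anchor is indirect: the Background quotes HR 0.56 for anti-PD1 and 0.51 for BRAF/MEK inhibition, each against placebo. The ratio is 0.56/0.51 = 1.10, from different populations and so only indicative.

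| Covariate (share) | HR | Dropped, 37–46 events |
|---|---|---|
| Therapy (30% or 50%, assumed) | 1.10 | 88–89% |
| | 1.3 | 77–81% |
| | 1.5 | 61–69% |
| Stage, split 50/50 (assumed) | 1.5 | 61–66% |
| | 1.75 | 40–48% |
| | 2.0 | 24–32% |
| | 2.5 | 7–13% |
| Stage IIIa–b versus the rest (9%/91%) | 2.0 | 62–67% |
| | 2.5 | 45–52% |

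The 9% comes from the protocol: 165 pre-included × 25% in IIIa–b × 30% node-positive = 12.4 patients, and 12.4/136 = 9%. For 80% retention, a balanced covariate needs an HR of about 2.1–2.3.

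**Effect on the ctDNA estimate.** Two simulations of 124 patients with no true ctDNA effect:
- Balanced stage with HR 1.5–2.0, ctDNA positivity 35% versus 15% by stage, therapy HR 1.2, about 47 events, 2,000 trials per setting. Type I error was 4.7–5.3% with the screen and 4.4–5.0% with stage and therapy forced in.
- Stage HR 1.6–2.0, ctDNA–stage odds ratio 3–5, therapy HR 1.4, six noise variables, about 35–37 events, 1,500 trials per setting. The average ctDNA HR was 1.02–1.05 with the screen against 1.00–1.01 with a fixed set, and the rejection rate 0.045–0.051 against 0.040–0.051. Stage was dropped in 35–61% of trials; in the same settings with a ctDNA HR of 2.5 it was dropped in 14–41%. About 0.6 noise variables entered, which is simply 6 × 0.10.

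**The case against.** The strongest defence is that the two sentences belong together: the first states an aim, the second the means, and therapy is only a candidate. That is a fair reading of the linking words. It turns a flat contradiction into a promise the method does not secure, because the adjustment still fails whenever therapy fails the screen.

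Several stronger readings are tempting, and the documents do not support them.
- *The screen distorts the primary result.* The log-rank comparison is untouched, and the simulations show almost no change in type I error or in the average ctDNA hazard ratio.
- *Therapy will usually, and stage often, be lost.* This rests on assumed effects. A balanced stage split with HR 2.5 would be kept about nine times in ten. A therapy effect near 1.1 would be dropped often, but its omission would change little. Therapy also cannot have influenced a sample drawn before it starts.
- *The primary hazard ratio must show that ctDNA predicts independently of other factors.* The protocol states that aim only for the time-dependent analysis, which carries no screen. For the primary analysis the commitment is adjustment.

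It can also be said that the planned comparison of baseline characteristics by ctDNA status will make imbalance visible. It will, but nothing in the text carries that result into the Cox model.

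What stands is the mismatch between commitment and rule, and an adjustment set decided by a low-power filter.

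**Conclusion.** The point holds in a limited form. The text commits to adjustment and then applies a rule that guarantees a place only to ctDNA. At the 37–46 events implied by the protocol's own figures, the screen is weak for moderate effects: it drops therapy in about 60–90% of trials for HR 1.1–1.5, and a balanced stage split in about 24–66% for HR 1.5–2.0. These rates rest on assumed hazard ratios and shares. Stage becomes reasonably safe only when its effect is large and its categories balanced (7–13% dropped at HR 2.5).

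The harm is to reproducibility and interpretation, not to error control. The adjusted hazard ratio depends on which variables happened to pass, and a reader cannot be sure it is adjusted for the factors the protocol's own Background links to ctDNA. The change is worth making because it costs little; the primary comparison is not invalid without it. It concerns a rule the article states, so a separate analysis plan that followed this text would carry the problem forward.

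**What to change.** - Delete the p<0.10 screen for the primary Cox model. Pre-specify post-operative ctDNA, type of adjuvant therapy and disease stage as forced covariates.
- Fix the stage coding in advance so that no category is sparse. A separate IIIa–b group would hold about 12 of 136 patients, or 12.4 × 0.30 = 3.7 events at the average rate and fewer if these patients are at lower risk. Stage III versus IV, or an ordered stage score, avoids this. The protocol does not give the III/IV split, so check the coding against baseline counts before any outcome is examined.
- Keep any larger or screened model as a sensitivity analysis.
- Use the same fixed set for the analyses that reuse this approach: pre-surgery ctDNA, copy number and its variation, and DMFS. Use fewer covariates for melanoma-specific survival if those deaths are few.

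The cost is a sentence or two of text and two or three degrees of freedom, which 37–46 events can support. Staging, pathology and treatment are already part of the study record, so no new data are needed.

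### The follow-up Cox model leaves out post-surgery ctDNA, so it cannot show that the later course of ctDNA is prognostic beyond the post-operative sample

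*Protocol article*

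**What the plan says.** The protocol article's Statistical analysis section models follow-up ctDNA "by considering mutated DNA copy number as a time-dependent variable in the Cox model". It then names the adjusters: "This analysis will be adjusted for baseline patient characteristics and for the type of adjuvant therapy". The purpose follows in the same sentence: "to assess whether the course of ctDNA during follow-up is an independent prognostic factor for survival". DMFS is to be handled in the same way as RFS.

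Post-surgery ctDNA is not listed for this model. Three places suggest that it is not meant to fall under baseline characteristics:

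- The primary model, in the same section, adjusts for the same two groups of covariates and brings in post-surgery ctDNA as a separate term.
- Objectives uses baseline ctDNA for the sample taken before surgery.
- Later in Statistical analysis, baseline characteristics are compared between patients with and without detectable ctDNA before or after surgery.

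The sample size section makes post-surgery ctDNA the central prognostic variable: "Our hypothesis is that 25% of patients will have detectable ctDNA post-operatively", and "a total of 124 patients would be required to achieve a hazard ratio of 2.5".

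**The concern.** The primary objective already tests the single post-operative sample. What the follow-up analysis could add is whether serial samples carry further prognostic information, which bears on the molecular-relapse concept in the Background and Discussion.

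If post-surgery ctDNA is prognostic, as the trial assumes, and patients who are positive tend to stay positive, then current ctDNA is a proxy for the post-surgery result. The planned term can be significant even when later measurements add nothing. Reading *independent* as including independence from the post-operative result would then be unjustified, and serial sampling could be credited with information that one sample already supplies.

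Post-surgery ctDNA is measured before the follow-up samples. It is therefore a possible confounder of the follow-up term and not an intermediate step, so adjusting for it is legitimate.

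**Working it through.** **Inputs from the sample size section.** 124 analysable patients, 25% ctDNA-positive after surgery, hazard ratio (HR) 2.5, 24-month RFS 70%, alpha 5% (taken as two-sided), power 90%, and an allowance for "10% of patients lost to follow-up at 24 months or not analysable". **From the sampling schedule:** draws every 3 to 4 months for a year, then every 6 months. **Not in the documents, so assumed:** how often post-surgery positives are positive later, and how often negatives turn positive.

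**1. The plan's own figure.** Freedman's formula with allocation ratio k = 1/3 (positive to negative) gives

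d = (1.96 + 1.2816)² × (1 + k·HR)² / [k·(HR − 1)²] = 10.51 × 1.833² / (0.333 × 2.25) ≈ 47.1 events.

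Reading the 70% as RFS in ctDNA-negative patients, the event share over 24 months is 0.75 × 0.30 + 0.25 × (1 − 0.70^2.5) ≈ 0.373. Then 47.1 / 0.373 gives about 127 patients, against 124 stated. The inputs are being read in a way close to the plan's. The article gives no figure for the follow-up model.

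**2. The mechanism by hand.** Let the hazard depend only on post-surgery status: 2.5 if positive, 1 if negative. Suppose positives are detected at a later visit with probability p and negatives with probability 5%. At the start of follow-up:

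| p | Share post-surgery positive among currently positive | Same among currently negative | Apparent HR for current ctDNA |
|---|---|---|---|
| 100% | 0.25/(0.25 + 0.0375) = 0.870 | 0 | 2.304/1 = 2.30 |
| 80% | 0.20/(0.20 + 0.0375) = 0.842 | 0.05/(0.05 + 0.7125) = 0.066 | 2.263/1.098 = 2.06 |
| 50% | 0.125/(0.125 + 0.0375) = 0.769 | 0.125/(0.125 + 0.7125) = 0.149 | 2.154/1.224 = 1.76 |
| 5% (no persistence) | 0.25 | 0.25 | 1.00 |

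Each hazard is 1 + 1.5 × the share. Within either post-surgery group, the HR for current ctDNA is exactly 1.

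**3. How often the term is significant.** Trials were simulated with N = 124, HR 2.5 for post-surgery status only, visits at 0, 3.5, 7, 10.5, 12, 18 and 24 months, no relapse-triggered draw, and a two-sided 5% test. With overall 24-month RFS of 70%, a 5% sporadic-positive rate and 600 trials per cell:

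| Detection at each visit in positives | 100% | 80% | 50% |
|---|---|---|---|
| Log copies, planned model | 62% | 50% | 28% |
| Presence, planned model | 67% | 50% | 28% |
| Raw copies, planned model | 28% | 23% | 13% |
| Any scale, post-surgery status added | 4–7% | 5–6% | 5–7% |

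A second simulation allowed 10% loss and let positivity fade from draw to draw. On log copies, a chance of staying positive of 0.6 / 0.8 / 0.9 / 0.95 per draw gave about 12% / 21–25% / 35–38% / 48–60%. Raw copies gave 9–25%. Using the HR of 1.87 that the Discussion cites for another adjuvant cohort, the rates were 8–30% (log) and 7–17% (raw).

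Two controls confirm the cause. With no persistence the rate was 3%; with post-surgery ctDNA not prognostic (HR 1.0) it was 3–5%. With post-surgery presence in the model it was 3–7% throughout.

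**4. What adjustment costs.** Here current status truly drives the hazard (presence term, about 37 events, 400 trials per cell). Power at HR 3 / 4 / 5:

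| Persistence | Planned model | Post-surgery status added | Loss in points |
|---|---|---|---|
| 50% | 79 / 95 / 98% | 66 / 88 / 95% | 13 / 7 / 3 |
| 80% | 89 / 98 / 99% | 51 / 68 / 83% | 38 / 30 / 16 |
| 100% | 91 / 98 / 100% | 33 / 46 / 56% | 58 / 52 / 44 |

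The loss grows with persistence because the two terms become nearly collinear. Inflation and loss of power are therefore largest in the same settings.

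**The case against.** **The plan asks a different question.** The sentence can be read as defining *independent* by its own adjusters, that is, independent of clinical factors and treatment. No objective explicitly asks for information beyond the post-operative sample. This stands in part. Whether current ctDNA predicts recurrence is a legitimate question, and the planned model answers it. A reader might infer from the table that the planned test has a type I error of up to two thirds. The documents do not support that: in these scenarios current ctDNA really is associated with RFS given the clinical covariates, so rejecting the planned null is correct. The percentages measure how often the result would mislead someone who took it as evidence about the added value of follow-up.

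**The size is assumed.** The documents give no persistence figure. They also name copy number without a log transform, and inflation is smaller on raw copies. This stands, and is why ranges are given. Rates above 50% need persistence of roughly 80–90% or more on log copies or presence.

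**Covariate lists belong in the full protocol or analysis plan.** The article does not enumerate baseline characteristics. The post-operative draw precedes inclusion, from which RFS is counted, and the Discussion uses baseline ctDNA for a resected cohort. Post-surgery ctDNA could therefore be on a fuller list. If it is, only the article's wording needs attention. As written, the article states the adjusters and the inference, and the primary model's separate naming of post-surgery ctDNA points the other way.

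**Conclusion.** The point holds as a limit on what the follow-up model can support. As written, a significant term does not show that the course of ctDNA is prognostic independently of the post-operative result. If only post-surgery status matters, the term would be significant in roughly 10–65% of trials on log copies or presence and about 9–28% on raw copies, at HR 2.5 and assumed persistence of about 50–100%. The rate is near 5% with no persistence and 3–7% once post-surgery ctDNA is in the model.

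The structural point does not depend on the exact rate; it needs only that post-surgery ctDNA be prognostic and persist to some degree. A reader might go further and conclude that the adjusted model should replace the planned one at little cost. The power figures do not support that. This is an inexpensive improvement to a secondary analysis and leaves the primary analysis untouched.

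**What to change.** - Keep the planned time-dependent model for RFS and DMFS. Report it as the association of current ctDNA level with outcome, adjusted for clinical factors and treatment.
- Add one prespecified model that also includes post-surgery ctDNA as a fixed covariate, as presence or log copies. Log copies may be preferable if risk depends on quantity, since presence alone could then leave residual confounding (not simulated).
- Make any claim that the follow-up course is prognostic independently of, or beyond, the post-operative sample only from that model, with its hazard ratio and confidence interval.
- State in advance that a non-significant adjusted term does not show that monitoring adds nothing.
- The interaction tests on the course of ctDNA need not move to the adjusted model.

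The change takes a sentence or two and one covariate already collected; a missing post-operative blood test is a listed ground for withdrawal, so few values should be absent. There are no extra visits, samples or patients. The price is lower power for the adjusted term: about 13 points at HR 3 and less at higher HRs if persistence is 50%, about 16–38 points at 80%, and about 44–58 at 100%.

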## Objectives

The primary objective of PERCIMEL study is to evaluate the predictive value of the presence of ctDNA post-surgery on recurrence-free survival at 24 months in patients undergoing surgery for cutaneous melanoma and treated with immunotherapy or targeted therapy with BRAF and MEK inhibitors, in an adjuvant setting.

The secondary objectives are:To evaluate the predictive value of baseline (prior to surgery) ctDNA on survival (recurrence-free survival, distant metastasis-free survival and specific survival).To analyse the quantitative and clonal course of ctDNA during 24 months of follow-up, or at relapse, to predict survivalTo describe the clinical characteristics and the quantitative course of ctDNA during follow-up in patients with no detectable ctDNA at pré and/or post-surgeryTo determine the predictive value of ctDNA course in subgroups of patients according to clinical and tumour characteristics at inclusion.

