### Follow-up visits during adjuvant therapy (up to 12 months)

All follow-up visits will be scheduled to coincide with the standard follow-up appointments, i.e. every 3 to 4 months ± 2 weeks, in order to avoid the patient having to attend visits solely for the purposes of the study.

Each follow-up visit will include:Complete clinical examinationAssessment of general state (WHO score) and body weightBiology, including complete blood count, hemostasis, blood gases, plasma creatinine, liver function tests, and any other biological parameter required for the implementation of adjuvant medical therapy.Recording of any adverse events grade > 2 or adverse events of any grade (according to the CTCAE classification version 5) if the impact on medical therapy or further management is significantRecording of concomitant treatments (if there are any changes compared to those recorded at the pre-inclusion visit)Tumour assessmentA blood draw of 30 ml for ctDNA analysis, performed on the day of each follow-up visit

In case of relapse during the 12 months of follow-up, the patient will have one final 30 ml blood draw and will then exit the study.

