### Follow-up visits (from 12 to 24 months)

All follow-up visits will be scheduled to coincide with the standard follow-up appointments, in order to avoid the patient having to attend visits solely for the purposes of the study. Follow-up visits will be planned according to current guidelines. For the purposes of the study, a follow-up visit will be planned every 6 months ± 2 weeks.

Appropriate, systematic radiological examination (CT or PET scan) is recommended every 6 months during the 12 months of follow-up.

Each follow-up visit will consist in:Complete clinical examinationAssessment of general state (WHO score) and body weightRecording of any adverse events grade > 2 or adverse events of any grade (according to the CTCAE classification version 5) if the impact on medical therapy or further management is significantRecording of concomitant treatments (if there are any changes compared to those recorded at the pre-inclusion visit)Tumour assessmentA blood draw of 30 ml for ctDNA analysis, performed on the day of each follow-up visit

After the 12 months of follow-up, the patient will have one final blood draw and will then exit the study.

In case of relapse during the 12 months of surveillance, the patient will have one final blood draw and will then exit the study.

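### If time runs forward and the relapse draw is included, the mixed model of ctDNA course in initially undetectable patients cannot show whether ctDNA rises before relapse

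*Protocol article*

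**What the plan says.** Under Objectives, one secondary aim is to describe "the quantitative course of ctDNA during follow-up in patients with no detectable ctDNA" before and/or after surgery. The Statistical analysis section carries this out as follows:

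- Method and patients: "In patients with no detectable ctDNA either pre- or post-operatively, the course of quantification of ctDNA will be described by repeated measure ANOVA", using a linear mixed model on mutant copy number.
- Terms: "Time will be considered as a fixed effect, and the patient as a random effect".
- Split by later outcome: "The analysis will be performed in patients who have progressive disease, and those who do not".
- End of each series: "The cut-off timepoint for this analysis will be the date of progression or end of follow-up".
- Data used: "taking account of all values obtained since inclusion".

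The visit sections fix how a relapser's series ends. During adjuvant therapy, "the patient will have one final 30 ml blood draw and will then exit the study". In the second year, "In case of relapse during the 12 months of surveillance, the patient will have one final blood draw" and then also leaves the study. The blood-draw section lists a sample at relapse as well. The Tumour assessment section lets the assessment that shows progression come before the visit at which the final sample is taken.

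Prediction of recurrence from the ctDNA course is handled elsewhere in the Statistical analysis section, by a Cox model with copy number as a time-dependent variable.

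**The concern.** Progressors relapse at different times and leave the series when they do. On an axis that runs forward from inclusion, each later visit holds only those who have not yet relapsed, and a growing part of its values comes from the relapse draw. The fitted course in progressors therefore mixes two things: how ctDNA behaves before relapse, and how many of the values at a visit were taken at relapse. A marker that stays at background until relapse gives a rising curve, and so does a marker that turns positive months earlier.

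This matters because the Background aims to find out whether ctDNA monitoring anticipates relapse, and the article's own planning figure puts about 75% of patients in the post-operatively undetectable group. This model is the only analysis dedicated to that group's later course. A reader who sees a significant rise in progressors and none in the others could easily take it as evidence of early warning.

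**Working it through.** **Inputs from the article.** Visits every 3 to 4 months to month 12, then every 6 months to month 24; a maximum of 9 draws; 25% ctDNA-positive after surgery; 70% recurrence-free at 24 months; hazard ratio 2.5; 124 patients, or 136 after allowing for losses.

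**Assumptions not in the article.** The distribution of relapse times, detection of relapse at the scheduled visits, the share of relapsers positive at relapse, the copy level at relapse, and the background level.

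**1. Draw count.** Three-monthly visits give 3 (before surgery, post-operative, start of adjuvant therapy) + 4 (months 3, 6, 9, 12) + 2 (months 18, 24) = 9, the stated maximum. Four-monthly visits give 3 + 3 + 2 = 8. The stated maximum thus fits a relapse draw that closes the visit series rather than adding to a full one.

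**2. Number of progressors.** With S the 24-month recurrence-free proportion in ctDNA-negative patients, 0.75·S + 0.25·S^2.5 = 0.70 gives S = 0.764. Then 0.75 × 136 = 102 negative patients and 102 × 0.236 ≈ 24 relapsers; from 124 patients, 93 × 0.236 ≈ 22.

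**3. Share of relapse draws among progressors' values.** With d_k relapses found at visit k, the share is d_k / Σ(d_j, j ≥ k).

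| Month | Uniform relapse times | Constant hazard | Hazard three times higher in year 1 |
|---|---|---|---|
| 3 | 3/24 = 12.5% | 14% | 21% |
| 6 | 3/21 = 14% | 16% | 25% |
| 9 | 3/18 = 17% | 18% | 32% |
| 12 | 3/15 = 20% | 21% | 44% |
| 18 | 6/12 = 50% | 52% | 51% |
| 24 | 6/6 = 100% | 100% | 100% |

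**4. What this does to the visit means.** For a marker that gives no warning, the expected mean at visit k is b + s_k × R, where b is background, s_k the share above and R the average excess at the relapse draw. Take 80% positive at relapse with a median of 10 copies/ml. This gives a relapse-draw mean of 13.3, a background of 0.16 and R = 13.14. Under constant hazard:

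- month 3: 0.16 + 0.14 × 13.14 = 2.00
- month 12: 0.16 + 0.21 × 13.14 = 2.92
- month 18: 0.16 + 0.52 × 13.14 = 6.99
- month 24: 0.16 + 13.14 = 13.30

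Simulated means at these months were 1.96, 3.01, 6.89 and 13.73. The rise is shallow to month 12 and steep after it.

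**5. How often the time effect is significant.** Random-intercept model, linear forward time, likelihood-ratio test at 5%, 25 progressors, 300 runs per setting, no warning before relapse. Entries are runs with a significant rise.

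| Positive at relapse | Scale | Relapse draw included | Relapse draw left out |
|---|---|---|---|
| 50% | raw copies | 75% | 4% |
| 50% | log | 90% | 3% |
| 80% | raw copies | 89% | 1% |
| 80% | log | 100% | 3% |

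With no signal even at relapse, the figure is 3%.

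A separate simulation (150 runs per setting) gave these rejection rates for categorical / linear time, again with no warning:

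- 22 progressors, 70% positive: 94% / 99%
- 22 progressors, 50% positive: 81% / 89%
- 22 progressors, 70% positive, three quarters of relapses in year 1: 80% / 93%
- 12 progressors, 70% positive: 72% / 85%
- 12 progressors, 50% positive, relapses concentrated in year 1: 48% / 53%

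Without the relapse draw these fall to 4 to 13%. With a true three-month lead and 22 progressors, the model rejects in 89 to 100% of runs, which overlaps the no-warning rates.

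**6. The same no-warning data counted back from relapse.** Using the values in step 4, the mean is 13.3 copies/ml at relapse and 0.16 at every earlier draw. This axis shows correctly that there was no lead.

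**The case against.** The strongest reply is that the model is not asked to establish lead time. The objective and the analysis text both speak of description, and prediction is given to the time-dependent Cox model, which is not restricted to ctDNA-positive patients. That stands. A reader might infer that the plan's test of whether ctDNA predicts relapse is compromised; the article does not support this. Description does not fully shield the model, however: the section closes with a general 5% significance threshold and exempts no analysis.

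A reader might also treat the rejection rates as false-positive rates. They are not. In the simulated relapsers ctDNA does go from background to positive by relapse, so rejecting no change over time is correct. What fails is placing the rise before relapse or at it.

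Two links in the argument are not settled by the text. First, if progression is dated at a tumour assessment that precedes the final draw, that draw may fall after the cut-off, and the effect disappears. The instruction to use all values points the other way but does not decide it. Second, the forward axis is read from the reference to inclusion; no time origin is stated.

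It would be too strong to say that late visits consist of relapse draws: that is so only at month 24, and about half at month 18 under all three relapse patterns. Nor does the article say that patients lost early are classed as non-progressors.

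Finally, a fixed three-monthly grid counted back from relapse would not suit six-monthly draws in the second year, and a reversed axis still groups by outcome. Both objections are fair and limit what the remedy should claim.

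**Conclusion.** The point holds in conditional form. If time runs forward from inclusion and the relapse draw enters the model, the time effect in progressors can be significant whether ctDNA rises only at relapse or months before it. The model then cannot show whether ctDNA precedes relapse in initially undetectable patients.

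With a no-warning marker, a significant time effect appeared in 75 to 100% of runs with 25 progressors and in about half to 85% with 12. The smaller number is relevant because the wording on pre- and post-operative undetectability can be read to define a smaller subgroup. The exact rates depend on the assumed positivity, copy level and relapse pattern. The rising share of relapse draws needs only staggered relapse times and exit at relapse.

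The consequence is confined to one descriptive secondary analysis. The primary analysis and the time-dependent Cox model are unaffected. The change is worth making because it is cheap and lets this analysis address a question the Background raises.

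**What to change.** Amend the mixed-model paragraph of the Statistical analysis section as follows:

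- State that the relapse draw, including one taken at a visit after the dated progression, is shown as a separate point and left out of the test of the time effect.
- Describe progressors on actual time before progression, either as continuous time or in windows that fit 3- to 4-monthly draws to month 12 and 6-monthly draws after. Report the number of patients contributing to each window.
- Show non-progressors at comparable elapsed time as a descriptive reference. Formal matching to pseudo-dates is optional.
- Keep the forward-time plot, without a test.

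No new samples, visits or patients are needed. The cost is a few sentences and some extra programming. The downside is sparse windows close to relapse for second-year relapsers, whose previous draw is about six months earlier. Windows far from relapse will come only from late relapsers, so the numbers per window should be read with the curve.
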